The hospitalisation rate consists of two elements: the number of hospitalisations and the period (in years) over which patients are followed up. We conducted simulations using the paramtest software package [76], computing 10′000 iterations of the chosen parameters. Based on the USB’s available data, we set the hospitalization events per patient year to 1.56. The study’s observation period is 15 months (1.25 years). We determined the minimum sample size using the inverse of the effect size in Schenkel et al. [6], i.e., 1.79 [1.31–2.43]. Following Olivier et al.’s guidance [77], we aimed for the upper bound of a small effect size. The simulation is based on a binomial distribution with a shape parameter of 4. Assuming an α level of 0.05, a power of 80% and an effect size of 1.79, a minimum sample size of 52 patients (26 per group) was determined. Based on a refusal rate of 10% and a 15% drop out rate, then, we will aim to recruit a total of 80 patients (40 per group). Considering that approximately 70 adults per year receive *both alloSCT and follow-up* at USB, recruitment will take a minimum of 16 months.

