#### Intervention group (IG)

The intervention, i.e., the SMILe-ICM as described above and shown in Fig. 2, will be delivered by eHealth and care coordinators (CCs). The four CCs will be specially-trained APNs. In addition to holding Master’s degrees in nursing, all CCs will be experienced alloSCT experts. Prior to study start, a six-day training segment has been provided by the USB’s SMILe project leader (SV, shared first author) in March 2021. The IG participants will receive care as usual *PLUS* the SMILe-ICM (as described above).

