**IMPLEMENTATION OUTCOME DATA (from intervention group / care coordinator team)**												
Acceptability	AIM (4 items) [90]	**X**	**X**	**X**	**X**	**X**	**X**	**X**	**X**	**X**	**X**	
Appropriateness	IAM (4 Items) [90]	**X**	**X**	**X**	**X**	**X**	**X**	**X**	**X**	**X**	**X**	
Feasibility	FIM (4 items) [90]	**X**	**X**	**X**	**X**	**X**	**X**	**X**	**X**	**X**	**X**	
Technology feasibility	N (days with data entry), N (technical problems)											
Intervention fidelity	N (visits), Minutes (visits), N (Behavioural Change Techniques) compared to protocol											
Intervention fidelity	5% of intervention sessions will be randomly selected to be audiotaped and checked for protocol congruence											

*Abbreviations. AIM* Acceptability of Intervention Measure, *BAASIS* Basel Assessment of Adherence to Immunosuppressive Medication Scale, *CRF* case report form, *FIM* Feasibility of Intervention Measure. *IAM* Intervention Appropriateness Measure, *MEMS* Medication Event Monitoring System, *PETS* Patient Experiences with Therapy and Self-management, *Tx* transplantation

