#### Implementation outcomes and evaluation of implementation pathway

After each of the 12 personal consultations, implementation outcomes (i.e., acceptability, appropriateness, feasibility, and fidelity) will be assessed using quantitative methods via surveys of intervention patients and of the CCs (APNs), who provide the SMILe-ICM (Table 4). The implementation pathway will be evaluated via a qualitative approach after the intervention period with input from the entire alloSCT team and all intervention patients.

**Table 4 Tab4:** Implementation outcomes

Outcome variable(s)	Measure(s) and data collection procedures	Data source and reporter (when applicable)
**Acceptability from patient’s perspective**	Acceptability—reflecting the end users’ satisfaction with the intervention—will be assessed using the 4-item Acceptability of Intervention Measure (AIM). Each item applies a 5-point Likert-type scale ranging from 1 (completely disagree) to 5 (completely agree) with higher scores indicating greater acceptability [90].	Paper survey (pat.)
**Appropriateness from patient’s perspective**	The intervention’s appropriateness, i.e., its perceived suitability to address problems within its target setting, will be assessed via the 4-item Intervention Appropriateness Measure (IAM). Each item applies a 5-point Likert-type scale ranging from 1 (completely disagree) to 5 (completely agree) with higher scores indicating greater appropriateness [90].	Paper survey (pat.)
**Feasibility from patient’s perspective**	The intervention’s perceived suitability for everyday use – will be assessed with the Feasibility of Intervention Measure (FIM). Each item applies a 5-point Likert-type scale ranging from 1 (completely disagree) to 5 (completely agree) with higher scores indicating greater feasibility [90].	Paper survey (pat.)
**Technology acceptability**	The ratio of the number of data entry days to the number of technological problems, will be a measured using data gathered via the SMILeApp.	SMILe monitoring data base (SMILe Care)
**Acceptability from CC’s perspective**	Acceptability—reflecting the end users’ satisfaction with the intervention—will be assessed using the 4-item Acceptability of Intervention Measure (AIM). Each item applies a 5-point Likert-type scale ranging from 1 (completely disagree) to 5 (completely agree) with higher scores indicating greater acceptability [90].	Paper survey (CC)

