#### Analysis

Statistical analyses will be conducted at the University of Basel’s Institute of Nursing Science using the R software package [96]. Data cleaning will include systematic screening for out-of-range values and data inconsistencies. Multiple imputations will be considered for missing data. Descriptive statistics will be applied as appropriate for all variables.
***Aim 1a:*** To determine whether hospitalisation rates (primary outcome) are reduced via the SMILe-ICM’s implementation, we will analyse any differences between IG and UCG rates by applying generalised linear mixed models (GLMM) [97]. The relevant variables (i.e., time, study group, and group x time interaction) will be entered into the models. Our targeted test statistic is the rate ratio by unconditional maximum likelihood estimation (Wald) as described by Rothman et al. [98] and implemented in epitools [99]. We will conduct intention-to-treat and per-protocol analysis. Two-sided significance will be set at 0.05. To analyze the target secondary outcomes over the course of time, descriptive analyses will be carried out and GLMM will be used to determine differences between the IG and UCG. Cost data will be collected and analysed quarterly. Overall survival will be analysed using the Kaplan-Meier method and the log-rank test. To analyse QALY, we will use the EQ-5D-5L**©** value set for Germany. The electronically compiled dosing history will be analysed using by applying GLMM, which account for dependence among observations from a single patient over time. The resulting estimates will be expressed as odds ratios (ORs) [100].
***Aim 1b:*** To test a potential wane-out effect of the SMILe-ICM’s intervention effect over 3 months’ post-intervention follow-up, differences between the IG and the UCG will be determined by applying GLMM. This approach allows calculation of the main group and time effects, and of group-by-time interaction effects. Two-sided significance will be set at 0.05.

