***Aim 2:*** Acceptability of Intervention Measure (AIM), Intervention Appropriateness Measure (IAM), and Feasibility of Intervention Measure (FIM) (implementation outcomes) [90] will be descriptively evaluated. Independent Student’s t-tests will be calculated to determine whether implementation outcome scores will change significantly within the IG over the study period. Concerning the analysis of the implementation pathway, field notes, audiotapes of interviews and mind maps of focus group discussions will serve as qualitative data. Transcript data will be stored and analysed in the ATLAS.ti 8 software package [101]. Individual interviews with patients will be thematically analysed following Braun et al.’s six-phase procedure—an approach using stepwise systematic and iterative processing of data to arrive at a meaningful description and interpretation [102]. During the focus group interviews with clinicians, key themes will be mind-mapped on a flipchart to help the researcher recall previous thoughts and summarise all of the focus groups’ input. Participants will have the opportunity to reflect on the maps and to add or change keywords [103]. After the final focus group session, all mind maps will be combined into a single meta-map using the Microsoft Visio Professional 2019 software [104]. We will then apply Mayring’s approach to qualitative content analysis [105].

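### Aim 2 plans independent-samples t-tests for change over time in AIM, IAM and FIM, although the same intervention patients give these scores repeatedly

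*Protocol article*

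**What the plan says.** The Analysis section (Aim 2) first has AIM, IAM and FIM evaluated descriptively, then adds an inferential step: "Independent Student’s t-tests will be calculated to determine whether implementation outcome scores will change significantly within the IG over the study period".

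Three other places show what kind of data these are.

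- Implementation outcomes and evaluation of implementation pathway: the timing is "After each of the 12 personal consultations, implementation outcomes", and the scores are "assessed using quantitative methods via surveys of intervention patients and of the CCs (APNs), who provide the SMILe-ICM".
- Table 2: AIM, IAM and FIM are marked at every visit from T0a to T8, which is ten time points, under the heading "IMPLEMENTATION OUTCOME DATA (from intervention group / care coordinator team)". The usual care group does not supply them.
- Intervention group (IG): "The four CCs will be specially-trained APNs".

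The same Analysis section uses generalised linear mixed models for Aim 1 and, for the electronic dosing history, gives within-patient dependence as the reason. No such model, and no paired test, is given for the Aim 2 scores.

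**The concern.** An independent-samples t-test treats the scores at two occasions as coming from two unrelated sets of people. Here they come largely from the same people, so the test leaves the covariance between occasions out of the standard error.

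No between-arm reading rescues the sentence. It asks about change within one arm over time, and only that arm has the scores.

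What is at stake is whether a change in acceptability, appropriateness or feasibility during the year is recognised. In the simplest use of the test, a real change, including a real decline, is more likely to be reported as non-significant than it should be. A two-sample test also does not fit a series of ten or more assessments, and the text does not name the occasions to be compared.

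**Working it through.** The documents give no sample size, power or error rate for Aim 2, so there is no stated figure to reproduce.

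**Inputs**

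- Intervention arm: 40, from "we will aim to recruit a total of 80 patients (40 per group)" (sample size section).
- Dropout: "Based on a refusal rate of 10% and a 15% drop out rate". 40 × 0.85 = 34.
- Alpha: "Two-sided significance will be set at 0.05" is stated for Aims 1a and 1b. None is stated for Aim 2, so 0.05 two-sided is assumed.
- Within-patient correlation ρ between two occasions: not given. Assumed 0.3, 0.5 and 0.7.

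**1. Standard error.** With n patients measured twice and equal standard deviation s:

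- independent test: SE = s·√(2/n)
- correct: SE = s·√(2(1−ρ)/n)
- ratio = 1/√(1−ρ) = 1/√0.7, 1/√0.5, 1/√0.3 = **1.20, 1.41, 1.83**

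**2. Type I error.** Under no change, the unpaired statistic has standard deviation √(1−ρ) instead of 1. In simulation (n = 40, 50,000 runs) the rejection rate at nominal 0.05 was about 0.021, 0.006 and 0.001. The paired t-test stayed between 0.048 and 0.052. Results for n = 34 were nearly the same.

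**3. Power.** Take a change that the paired analysis detects with 80% power, so that the true difference is 1.960 + 0.842 = 2.802 correct standard errors. The unpaired statistic then has mean 2.802·√(1−ρ) and standard deviation √(1−ρ), so

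power = Φ(2.802 − 1.960/√(1−ρ))

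- ρ = 0.3: Φ(2.802 − 2.343) = Φ(0.459) = **0.68**
- ρ = 0.5: Φ(2.802 − 2.772) = Φ(0.030) = **0.51**
- ρ = 0.7: Φ(2.802 − 3.578) = Φ(−0.776) = **0.22**

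Simulation with t-tests at n = 40 (100,000 runs) gave 0.69, 0.53 and 0.24. A common shortcut, Φ(2.802·√(1−ρ) − 1.960), gives 0.65, 0.51 and 0.34. It wrongly keeps the standard deviation of the statistic at 1, so it understates the loss at ρ = 0.7. The conclusion is the same.

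**4. A fixed shift.** For a change of 0.5 SD with n = 34, simulated power was 0.67, 0.81 and 0.96 for the paired test, against 0.54, 0.54 and 0.55 for the independent test.

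**5. Pooled visits.** The article does not say that visits will be pooled, but it does not exclude it. With five early visits compared with five late ones as independent rows (n = 40, 10,000 runs), the type I error was:

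| Correlation over time | Type I error at nominal 0.05 |
|---|---|
| Constant, ρ 0.3 to 0.8 | 0.021 down to below 0.001 |
| Decaying (AR(1)), ρ 0.3 to 0.8 | 0.11 to 0.16 |
| Random slopes, three assumed variances | 0.02 to 0.07 |

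The direction therefore depends on a contrast that the article leaves open.

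**The case against.** The best defence concerns weight. The scores are to be evaluated descriptively first, the t-tests are an addition, and no power or decision rule hangs on them. The Study aims section does not name change over time as part of Aim 2, and the Study design section makes effectiveness the central concern. For two time points the error is conservative, so it does not manufacture a finding. The correlations are assumptions, and the 80% reference power is illustrative because the article sets no such target. All of this stands. It limits the importance of the fault but does not make the test right.

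A reader might infer more than the documents support:

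- **That coordinator ratings will be t-tested as if independent.** Coordinators are surveyed, but the test sentence refers only to the IG, and Table 2 names the intervention group and the coordinator team separately. The point is conditional.
- **That better-scoring survivors will mimic improvement.** Nothing says that patients who die or stop score lower, and the Analysis section says that multiple imputation will be considered.
- **That each test uses two of ten time points.** No contrast is stated. The text's 12 consultations and Table 2's ten occasions also differ, although either way these are repeated measures.
- **That false positives are inflated.** This follows only under pooling combined with decaying correlation or sufficiently varying slopes.

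**Conclusion.** The point holds in a limited form. The named test is wrong as written for repeated scores from the same patients, and nothing else in the article supplies a valid alternative for them. For a two-occasion comparison the consequence is lost power: standard errors 1.20 to 1.83 times too large, and 80% power reduced to about 68%, 51% or 22%. These figures assume correlations of 0.3, 0.5 and 0.7, equal variances, complete pairs and a two-sided 0.05 level. The fault disappears only at zero correlation.

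It is confined to the inferential test of change in three scale scores. It would be too strong to say that Aim 2 as a whole is invalid: its descriptive, fidelity and qualitative parts do not depend on this test, and neither does any Aim 1 analysis. This should be fixed, but it does not threaten the trial's main conclusions.

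**What to change.** Replace the t-test sentence with a linear mixed model for each of AIM, IAM and FIM: time point as a fixed effect, a random intercept per patient, and the change from first to last assessment reported with a 95% confidence interval. This is in line with the mixed-model approach already planned for Aim 1. Because correlation may decay over the year, check that a random intercept alone describes it adequately. The minimum correction is a paired t-test between two time points named in advance.

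State which assessments count, so that the 12 consultations and the ten occasions in Table 2 are reconciled. If coordinator ratings are also to be tested, allow for clustering within the four coordinators. Otherwise report them descriptively only.

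The cost is a sentence or two in the Analysis section. No new data, visits or patients are needed.

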## Discussion

Many European countries, including Switzerland, promote innovation approaches to delivering outpatient care. As the demand for outpatient care grows, there is increasing tension on health care systems, due to volume and cost, based on principles of integrated care [29, 106–108]. The use of technology such as eHealth is common within policy agendas [109, 110]. In addition, emerging evidence regarding its capacity to deliver interventions for both acute and chronically ill patients will potentially accelerate innovation in integrated care delivery. eHealth-facilitated interventions can be effective on health- and cost-related outcome measures [9]. In addition to the potential of eHealth-facilitated interventions to reduce re-hospitalisation rates and shorten length of stay [111–113], such interventions can improve patients’ medical and behavioural outcomes in view of symptom severity, quality of life (QoL), medication adherence [7–11] and other behavioural performance measures [3, 114, 115]. While eHealth-facilitated ICMs have been tested in trial settings, their successful implementation in clinical settings remains a challenge [116–118]. Very limited work has focused on bundled implementation strategies to support their implementation and evaluating of implementation outcomes and implementation pathways is largely lacking. Additionally, it is not known which strategies (or bundles) are appropriate for a particular context.

This research shortfall hinders, delays and may even prevent successful translation and scaling-up of interventions to real-life clinical settings. Therefore, the SMILe–ICM—which, as noted, was developed by combining implementation-, computer-, and behavioural-science methods—will now be tested in a hybrid effectiveness-implementation RCT. If successful, in addition to bridging important gaps in view of clinical practice for alloSCT care, this model’s multi-field combination of elements will represent a major methodological innovation.

SMILe’s implementation will be guided by bundled, contextually-adapted implementation strategies. These strategies were determined by our contextual analysis, empirical evidence, theory, and stakeholder involvement. However, context is not static. On the contrary, context can change rapidly (e.g., personnel and/or leadership can change, a pandemic can strike) potentially defeating the best-prepared process. Our planned evaluation of the SMILe–ICM including the bundle of implementation strategies will use mixed methods to shed light on adaptations to strengthen the SMILe-ICM and the bundle of implementation strategies in future scale-up.

Issues with the model’s technology component may also arise. To counter this possibility, software components have been specifically developed for this project using an agile software development approach [61]. Agile development methodology is an iterative approach: working parts of the software are developed in close collaboration with stakeholders, and feedback is collected early. This enables regular and early user tests, each of which enhances the likelihood of acceptance and fidelity. Additionally, alongside the USB’s IT department, the SMILe project’s software development team has devoted considerable time and expertise to embedding the technology component very well within the USB’s IT ecosystem. Moreover, the SMILe software team will be closely involved in the evaluation of the SMILe-ICM, providing technological support where needed.

As important as any eHealth solution’s health benefits may be, ethical aspects are equally important. For example, to safeguard patients’ autonomy and privacy (121–124), data are pseudonymised, with only APNs having access to the patients’ private data. And patients will always have the possibility to actively block data exchanges pertaining to them, i.e., they can select whether their entered data can be viewed in SMILeCare, the transplant team’s monitoring platform (125). In an affiliated project, we will closely track any negative or ambiguous effects (125–127) of SMILe-ICM. I.e., the DARE project (new DAta new REsponsilities) [119] will provide insights into the ethical and social implications of eHealth solutions in general and SMILe in particular. Comprehensive exploration of this dimension is crucial to future digitalization processes and scaling-up either of the eICM or of any care models that involve eHealth components.

The current study includes some risk of contamination bias: while the SMILe–ICM will be tested in an RCT, after the patients are randomised into UCG and IG, they will receive their care from the same alloSCT team. To minimise this risk, the APNs/CCs will only have contact with the IG participants. While this approach will not fully exclude the possibility of contamination, it will reduce it to an acceptable level. Admittedly, a cluster randomised approach would reduce this risk further; yet, given the importance at this stage of the SMILe–ICM’s development of establishing its effectiveness, the RCT design will be adequate.

## Conclusion

The SMILe–ICM has the potential to bring true innovation to the current alloSCT follow-up approach by re-engineering it into an integrated, comprehensive, multidisciplinary eHealth-facilitated model of care supported by a bundle of implementation strategies. In addition to supporting fast and well-informed reactions to acute, sometimes life-threatening symptoms, the SMILe-ICM will support patients’ self-management. Developed by combining implementation-, computer- and behavioural-science methods, and now being tested using a hybrid effectiveness-implementation RCT, the SMILe–ICM fills important gaps both in alloSCT care and in implementation science methodology. If it proves effective, this implementation science study will have generated sufficient evidence to support translation and scaling up of the SMILe–ICM to other high-risk chronically ill populations and settings.

## Data Availability

Not applicable.

## Abbreviations

AlloSCT: Allogeneic stem cell transplantation
APN: Advanced Practice Nurse
CC: Care coordinator
eCCM: eHealth enhanced Chronic Care Model
eICM: eHealth-facilitated, integrated care model
EHR: Electronic health record
ePROs: electronic Patient Reported Outcomes
GLMM: Generalised linear mixed models
GvHD: Graft versus Host Disease
IG: Intervention group
RA: Research assistant
RCT: Randomised controlled trial
SMILe: Development/Adaptation, Implementation and Testing of an Integrated Model of Care for allogeneic SteM Cell TransplantatIon faciLitated by eHealth – An effectiveness, implementation science study
UCG: Usual care group
USB: University Hospital Basel
